## Abstract

**Introduction:**

Theoretical models of health behavior are important guides for disease prevention and detection, treatment and rehabilitation, and promotion and maintenance of physical and mental health, but there are no intervention studies related to differentiated thyroid cancer (DTC) that use theoretical models of health as a guide. In this study, we used a microblogging platform as an intervention vehicle and mobile patient-doctor interactive health education as a means of intervention, with the aim of improving the health behaviors of DTC patients as well as the corresponding clinical outcomes.

**Methods:**

This research project is a quantitative methodological study, and the trial will be a single-blind, single-center randomized controlled trial conducted at the Fourth Hospital of Harbin Medical University in Harbin, Heilongjiang Province. The study subjects are patients over 18 years of age with differentiated thyroid cancer who were given radioactive iodine-131 therapy as well as endocrine therapy after radical surgery for thyroid cancer. The intervention group will receive MTM-mhealth, and the realization of health education will rely on the smart terminal WeChat platform. Routine discharge education will be given to the control group at discharge. The primary outcome will be change in thyroid-stimulating hormone (TSH) from baseline and at 3 and 6 months of follow-up, and secondary outcomes will include change in self-management behavior, social cognitive and psychological, and metabolic control.

**Discussion:**

This study will explore a feasible mHealth intervention program applied to a population of DTC patients using the Multi-theory model of health behavior change (MTM) as a guide, with the aim of evaluating the MTM-based intervention program for clinical outcome improvement in DTC patients, as well as determining the effectiveness of the MTM-based intervention program in improving self-management skills in DTC patients. The results of this study will indicate the feasibility as well as the effectiveness of the application of health theoretical modeling combined with mHealth applications in disease prognostic health management models, and provide policy recommendations and technological translations for the development of mobility-based health management applications in the field of health management.

## Introduction

1

Thyroid cancer can be divided into differentiated thyroid cancer and undifferentiated thyroid cancer according to tissue classification, in which differentiated thyroid cancer (DTC) develops in more than 90% of patients (1, 2), and the global incidence of thyroid cancer increased by about 20% from 1990 to 2013 (3). According to the Annual Report of China Tumor Registry, the incidence of thyroid cancer in China has continued to increase from 2008 to 2018, and the incidence is likely to continue to rise in the foreseeable future (4). Wiltshire et al. conducted a systematic review of studies in Europe, North America, Asia, Oceania, and South America, confirming that the overall incidence of thyroid cancer has continued to increase globally (5).

Surgical resection is the standard of care for most patients with DTC. In particular, low-risk patients with highly differentiated thyroid cancer can be treated with surgical resection only, without the need for excessive radiation therapy (6–8), whereas patients with high-risk features require thyroid-stimulating hormone (TSH) suppression and radioactive iodine therapy (RAI) in conjunction with each other (9, 10).DTC is a TSH-dependent tumor, and TSH is able to stimulate the expression of TSH receptors in normal thyroid cells and DTC cells, leading to abnormal proliferation of normal thyroid tissue and cancerous tissue that may remain, increasing the likelihood of recurrence (11–13). Therefore, TSH suppression therapy plays a crucial role in postoperative DTC, particularly for patients undergoing total or near-total resection. These patients require thyroid hormone supplementation to lower TSH levels after surgery, not only to compensate for hormone deficiencies but also to impede the growth of DTC cells and prevent recurrence (14–17). Consequently, the continuous self-management of DTC patients, guided by medical professionals, becomes pivotal for effective TSH suppression therapy. Unfortunately, the existing postoperative care measures are insufficient, leading to various disease-specific health issues following initial treatment (18–20). Thus, it is imperative to adopt more innovative and effective approaches to enhance the prevention and treatment of differentiated thyroid cancer, ultimately improving prognosis and reducing the risk of recurrence.

With the advancement of medical technology, there is an increasing demand for personalized and precise disease management in patients with thyroid tumors. Studies have shown that fatigue and insomnia are two of the most common symptoms in DTC patients, for whom self-monitoring of serum TSH levels should be proactive in order to achieve a favorable prognosis (21, 22). The definition of self-management is for patients to take on the task of managing their own health (9, 23). This self-management by patients by rationalizing their exercise, diet, routine and taking medication in a self-disciplined manner is one way to address this need and may have a crucial role in improving the cure rate of patients with differentiated thyroid cancer.

The development of mobile technology has led to the gradual popularization of social software such as WeChat, where communication between patients and physicians can be shifted from offline to online, in addition, the World Health Organization has called for the expansion of the use of digital technology to improve health support for patients, which have effectively contributed to the development of mobile health (mHealth) (24–28). As a result, mHealth is widely used by a large number of healthcare entities and plays an important role in the prevention and treatment of chronic diseases such as hypertension, diabetes, asthma, and postoperative rehabilitation of the heart and lungs and can save up to seven billion dollars in budgets annually (29, 30). The use of cell phones and mHealth apps continues to proliferate, with an increasing number of healthcare professionals, young and highly educated patients, and the general public using health apps (31–34). Evidence suggests that the use of mHealth apps can play an important role in patient education, disease self-management, remote monitoring of patients, and improvement of quality of life (35–37). For example, LianHong Wang et al. demonstrated that the Transtheoretical Model (TTM)-based mHealth apps can reduce body mass index and other physiological indicators in patients with polycystic syndrome, and improve the exercise and dietary adherence of polycystic syndrome patients in the long term (31–34). syndrome patients’ exercise and diet adherence (38). Basch et al. found that a convenient electronic system for cancer patients to query symptom outcomes could lead to early detection of symptoms and prompt clinicians to intervene (39). Therefore, we believe that mHealth intervention models can be well suited to the postoperative self-management environment for patients with differentiated thyroid cancer, which effectively reduces the stress on healthcare providers and improves patient recovery (40), and reduces patients’ fear of recurrence (41). In public health research, many interventions have helped to improve patients’ self-management level, but there is no study that uses the health theory behavior model as a guide to intervene in the self-health management level of differentiated thyroid cancer patients after surgery. In this study, we will use the WeChat platform as an intervention vehicle for mobile health interventions for DTC patients, with the aim of improving the health behaviors of DTC patients and the corresponding clinical outcomes.

Health behaviors are positive actions taken by individuals to prevent disease and maintain their own health, which include changing health-hazardous lifestyles, reducing or stopping health-risk behaviors (e.g., smoking, alcohol abuse, poor diet, and unprotected sexual behavior, etc.), adopting positive health behaviors (e.g., regular exercise, regular medical checkups, etc.), and complying with medical advice (42, 43). Theoretical models of health behaviors are important for disease prevention and detection, treatment and rehabilitation, and the promotion and maintenance of physical and mental health, but no intervention studies related to DTC have used theoretical models of health as a guide. Therefore, we aimed to evaluate a mHealth intervention study based on the Multi-theory model of health behavior change (MTM) (44–46) in anticipation of improving self-management in postoperative patients with differentiated thyroid cancer. The MTM divides behavioral change into two components: (1) initiation of behavior change (2) maintenance of behavior change. The initiation of behavior change is influenced by three factors: Participatory Dialog (PD), Behavioral Confidence (BC), and Changes in Physical Environment (CPE). The maintenance of behavioral change is influenced by three factors: Emotional Transformation (ET), Practice for Change (PC) and Changes in Social Environment (CSE) (Figure 1). Its role as a fourth-generation theoretical model used for health education (47–49) has been demonstrated to play an important role in health behavior change, such as smoking cessation (50), promotion of human papilloma virus (HPV) vaccination behaviors (51), and promotion of physical activity practice (47, 52). However, the application of MTM in the field of differentiated thyroid cancer is still in the exploratory stage, with fewer theoretical studies and applications.

**Figure 1 fig1:**
[figure not shown]
Schematic diagram of a multi-theoretical model of health behavior change.

In summary, given the great potential of health intervention models guided by the health behavior theory model for prognostic improvement in health care for a wide range of diseases, this study aims to MTM model to construct a health education intervention model for patients with DTC, and to provide a clinical rationale for mobile health intervention to assist in treatment plans related to prognostic rehabilitation of oncology patients by means of mobile patient-doctor interactive health education as a means of intervention.

Specific objectives are

To evaluate the impact of the Multi-theory model of health behavior change (MTM) interventions on clinical outcomes in patients with DTC.To determine the effectiveness of the MTM-based intervention program in improving self-management skills of DTC patients.

## Methods

2

### Study design

2.1

The study will be conducted from March 2023 to March 2024 using a quantitative methodology study with a measurement protocol that utilizes clinical reagent tests as well as internationally accepted scales to effectively ensure the objectivity of the trial. The quantitative investigation will be conducted as a randomized controlled trial in a hospital-based patient population compared to a routine education control group to compare the effectiveness of the MTM-based intervention program in patients’ TSH control and self-management behaviors (e.g., medication use, diet). The intervention group will receive the MTM-mHealth model intervention and the control group will receive usual care. The intervention will last for 3 months. Questionnaires and physical examinations will be conducted at baseline and at 3 and 6 months of follow-up to check for changes in self-management behaviors and TSH control. The flow chart of the study is shown in Figure 2 and Table 1.

**Figure 2 fig2:**
[figure not shown]
Flow chart of patient recruitment and study implementation.

**Table 1 tab1:** Timeline for study enrollment, intervention, and evaluation.

Study Period	Recruitment	Allocation	Intervention		Follow-up
TIMEPOINT	-T1	0	0 M	3 M	6 M
ENROLMENT: eligbility screen	√				
Informed consent	√				
Allocation		√			
INTERVENTIONS: MTM-mHealth					
Control					
ASSESSMENTS: sociodemographic variables			√		
Anthropometric variables			√	√	√
The MTM theory scale			√	√	√
The frequency of iodine-containing diets			√	√	√
Medication adherence			√	√	√
Social cognition and psychology			√	√	√

#### Study setting and randomization

2.1.1

This research project is a single-blind, single-center randomized controlled trial to be conducted at the Fourth Hospital of Harbin Medical University in Harbin, Heilongjiang Province, China. The study population is patients with differentiated thyroid cancer. Convenience sampling of patients with differentiated thyroid cancer was performed. Given that the proposed patient population is socially dispersed cancer patients, the patients coming to the hospital are far from meeting the trial needs of the minimum study sample size at one time, so the patients will be recruited in the form of consecutive enrollment, and the researcher will recruit the patients who have high adherence to the treatment when they come to the hospital on the same day. A random integer will be generated by the EXCEL function RANDBETWEEN for each patient registered on that day.

Given that the total number of patients registered at the hospital on the daily visit may be odd or even, in order to ensure the complete realization of randomized allocation, if the total number of registered patients on the day is even, we will use the random integer of two patients as a combination of numbers, and the groups will be compared, and divided into different groups according to the size of the corresponding random number (large, intervention group, small, control group); if the total number of registered patients on the day is odd, after removing the even pairs of patients, the remaining individual patients are judged by the parity attribute of their random numbers (odd, intervention group, even, control group), thus achieving randomized allocation.

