#### Approval of trial protocol and amendments

3.1.8

If the investigator fails to comply with the pre-established survey and follow-up criteria, the study leader will retain the authority to terminate the trial, revise the randomization protocol, and re-collect the data after the revisions have been completed. In the event of fundamental or widespread design errors or inaccuracies in the study questionnaire during the course of the investigation, the investigator will discontinue the trial and revise and redesign the questionnaire. After the necessary revisions have been completed, the revised questionnaire will be redistributed to patients.

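### On days with three or more patients, the allocation rule does not fix who is paired with whom, so a patient's arm can depend on a choice made after the numbers are seen

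*Protocol article*

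**What the plan says.** All of the allocation procedure is in section 2.1.1 (Study setting and randomization) of the protocol article.

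- **Who is recruited:** "the researcher will recruit the patients who have high adherence to the treatment when they come to the hospital on the same day".
- **Source of the numbers:** "A random integer will be generated by the EXCEL function RANDBETWEEN for each patient registered on that day".
- **Even daily total:** "we will use the random integer of two patients as a combination of numbers", and the two patients are "divided into different groups according to the size of the corresponding random number (large, intervention group, small, control group").
- **Odd daily total:** "after removing the even pairs of patients, the remaining individual patients are judged by the parity attribute of their random numbers", with odd going to intervention and even to control.
- **Blinding:** "This research project is a single-blind, single-center randomized controlled trial". The section does not say who is blinded.

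Table 1 places eligibility screening and informed consent at −T1 and allocation at 0. Section 2.2 says that recruitment began in March 2023.

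Section 3.1.8 (Approval of trial protocol and amendments) covers an investigator who does not meet the survey and follow-up criteria. In that case the study leader may terminate the trial, or "revise the randomization protocol, and re-collect the data after the revisions have been completed".

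**The concern.** The rule reads as complete, and the section concludes that it delivers randomised allocation. As described, identified patients come first, then their numbers, then the pairs. Once the numbers exist, a patient's arm is settled by which other patient they are compared with, or by being the one left over. The text settles neither point and does not require the pairs to be formed before the numbers are visible. A step that should be mechanical is left to whoever does the pairing.

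This matters more here because the same section has the researcher choose patients on perceived adherence. Medication adherence is a secondary outcome (section 2.7), and the introduction treats self-management as central to TSH suppression, the basis of the primary outcome. If patients thought more adherent were placed in the intervention arm more often, the comparison would be biased in its favour. In a trial of about 98 patients, no analysis could reliably undo that.

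**Working it through.** **1. The plan's own figure.** Section 2.3 gives target rates of 90% and 60%, two-sided α of 0.05, power of 90% and 20% loss. With unpooled variance:

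n = (1.960 + 1.282)² × (0.90×0.10 + 0.60×0.40) / 0.30² = 10.51 × 0.33 / 0.09 = 38.5, so 39 per arm.

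39 / 0.80 = 48.75, so 49 per arm and 98 in total. This reproduces. The allocation point does not affect it; 98 is used only in step 5.

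**2. Three patients, numbers 12, 57 and 83.** The rule permits any of them to be left over.

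| Left over | Leftover's arm (parity) | Pair compared | 12 | 57 | 83 |
|---|---|---|---|---|---|
| 12 | even: control | 57 v 83 | control | **control** | intervention |
| 57 | odd: intervention | 12 v 83 | control | **intervention** | intervention |
| 83 | odd: intervention | 12 v 57 | control | **intervention** | intervention |

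Patient 57 can be placed in either arm. Patients 12 and 83 cannot be moved in this example.

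**3. Four patients, numbers a < b < c < d.** There are three pairings.

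| Pairing | Intervention | Control |
|---|---|---|
| a–b, c–d | b, d | a, c |
| a–c, b–d | c, d | a, b |
| a–d, b–c | c, d | a, b |

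The highest number always goes to intervention and the lowest always to control. The two middle patients always land in opposite arms, but the pairing decides which goes where.

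**4. General case, m patients on a day, pairs formed after the numbers are seen, ties ignored.**

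- Even m: a given patient can be placed in the intervention arm unless theirs is the lowest number. The chance is (m − 1)/m. By symmetry it is the same for control.
- Odd m: placement in intervention fails only if their number is both the lowest and even. The chance is 1 − 1/(2m). Again it is the same for control.
- Share of patients whose arm is entirely open to choice: (m − 2)/m for even m and 1 − 1/m for odd m.

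| m | Chance that a given patient can be placed in a wanted arm | Share open to either arm |
|---|---|---|
| 1 | 50% | 0% |
| 2 | 50% | 0% |
| 3 | 83% | 67% |
| 4 | 75% | 50% |
| 5 | 90% | 80% |
| 6 | 83% | 67% |

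A simulation with 40,000 draws per m agreed with these formulas. If the pairs were fixed before the draw, the figures would be 50% and 0% for every m. The first column is for one chosen patient; several patients on the same day cannot all be placed independently, as step 3 shows.

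**5. How many patients this could touch.** Daily volume is not stated. Assume that 98 patients arrive at random (Poisson) over D recruiting days, with λ = 98/D. The share of patients on days with three or more is 1 − e^(−λ)(1 + λ).

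| D (assumed) | λ | Share | Patients of 98 |
|---|---|---|---|
| 365 | 0.268 | 3.0% | about 3 |
| 250 | 0.392 | 5.9% | about 6 |
| 125 | 0.784 | 18.5% | about 18 |

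**The case against.** The strongest reply is that a journal article condenses its protocol, so custody of the numbers and concealment may be described elsewhere. That holds for concealment mechanics, and silence on them is not the point here. It does not cover the pairing: the article sets out the rule step by step, and the rule as written gives more than one answer from the same numbers.

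The second reply is that the scope is small. This stands. On one- and two-patient days pairing gives no freedom, and under the assumed arrivals most patients fall on such days. On even-total days the extreme numbers cannot be moved.

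A reader might also infer more than the documents support:

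- *That numbers are drawn before consent, so a refusal breaks a pair.* Table 1 puts consent before allocation and section 3.1.5 requires consent before the trial starts. The word registered in section 2.1.1 could mean hospital or trial registration. It is unclear wording, not evidence of that order.
- *That recruiters know the arm or form the pairs themselves.* No section says so. Equally, none separates the two roles.
- *That section 3.1.8 shows that allocation can be steered.* Its authority is conditional. Section 3.1.4 sends revisions that need formal approval to the ethics committee, and section 3.1.9 lets the data monitoring committee suspend or stop the study for unauthorised changes. It is a separate issue.
- *That the spreadsheet numbers are bound to change on recalculation.* Nothing says that the values are not saved. Ties have no rule, but that is minor.

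**Conclusion.** The point holds in a limited form. The stated rule does not determine the arm on days with three or more patients, because the pairs, the leftover patient and the order of pairing and drawing are not fixed. On one- or two-patient days the only gap is that nothing locks the first draw.

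The possible reach is about 3% to 18.5% of patients, or roughly 3 to 18 of 98. This rests on assumed random arrivals over 365 to 125 days; more clustered attendance would raise it. The share that could actually be moved is smaller, since only some patients on those days are open to choice (67% with three patients, 50% with four). The 83%, 75% and 90% figures also assume that the person pairing has seen the numbers, which the text neither states nor prevents.

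A reader might conclude that allocation was steered or that the trial is biased. The documents do not show that. They show a rule that permits it, next to a recruitment step that already rests on judged adherence.

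**What to change.** **Preferred, for patients not yet randomised.** Replace the daily pairing with one list generated in advance, for example permuted blocks of mixed size. A team member who does not recruit should hold it. Each assignment should be revealed only after eligibility, consent and baseline data are recorded.

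**Minimum, if the present method is kept.** Fix the pairing order, for example by registration time, before any number is drawn; this also fixes who is left over. Save the first draw with no redraw, and add a rule for ties.

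**Patients already randomised.** Document the pairing order actually used on each day, state on which days three or more patients were allocated, and keep everyone in the assigned arm.

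**Separately, section 3.1.8.** Failure to meet survey or follow-up criteria should not trigger a revision of the randomisation. Remove that consequence from the clause.

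**Cost.** A short amendment, and a change of method during recruitment that must be reported. The preferred version needs a team member outside recruitment. The multidisciplinary team in section 2.5 may include one, but the article does not say so. The sample size is unaffected.
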